## Annex 1: CHW enrolment and activity form:

| **Biographic details** | | | | **Educational background** | | | | | | | | **ACTC CRT enrolment survey with CHWs**  *Instructions for use: Complete every question. Make sure that the answers are written clearly.* | |
| --- | --- | --- | --- | --- | --- | --- | --- | --- | --- | --- | --- | --- | --- |
| 1 | CHW ID number: CRT _ ClinicID_HP_CHW | [Insert study label] | | 6 | What level of schooling did the CHW complete? | | | No education | | | \|__\| |  |  |
|  |  |  |  |  |  |  |  | Informal / religious | | | \|__\| |  |  |
|  |  |  |  |  |  |  |  | Primary | | | \|__\| |  |  |
|  |  |  |  |  |  |  |  | Secondary | | | \|__\| |  |  |
|  |  |  |  |  |  |  |  | Higher | | | \|__\| |  |  |
| 2 | Health-Post MoPH No: | \|__\|__\|__\|__\|__\| | |  | | | | | | | |  |  |
| 3 | CHW Gender: | Female | \|__\| | 7 | Literacy level: | | | Illiterate | | | \|__\| |  |  |
|  |  | Male | \|__\| |  |  |  |  | Semi-literate | | | \|__\| |  |  |
| 4 | CHW age: | \|__\|__\|yrs | |  |  |  |  | Literate | | | \|__\| |  |  |
| 5 | Village CHW is based: |  | |  |  |  |  |  |  |  |  |  |  |
| **Job role** | | | | **CHW training** | | | | | | | |  |  |
| 8 | Length of time as CHW:  (Eg: 00yrs 09months) | \|__\|__\|yrs  \|__\|__\|mths | | 13 | Received initial training at beginning of CHW job? | Yes | | | | \|__\| | |  |  |
|  |  |  |  |  |  | No | | | | \|__\| | |  |  |
| 9 | Does CHW work with a partner? | Yes | \|__\| | 14 | Number of weeks spent on CHW initial training: | \|__\|__\| weeks | | | | | |  |  |
|  |  | No | \|__\| | 15 | Received any other CHW training whilst a CHW? | Yes | | | | \|__\| | |  |  |
|  |  |  |  |  |  | No | | | | \|__\| | |  |  |
| 10 | If yes to what is the partner’s ID number: | CRT-\|__\|__\|__\|-\|__\|__\|-\|__\| | | 16 | If yes to Q14, list the training received (for CHW role) and who provided the training: | Training Subject | | | | Training Provider | | No. Days | Year |
| 11 | Does CHW have another job as well as this job? | Yes | \|__\| |  |  |  | | | |  | | \|__\|__\| | \|__\|__\|__\|__\| |
|  |  | No | \|__\| |  |  |  | | | |  | | \|__\|__\| | \|__\|__\|__\|__\| |
| 12 | If yes to Q,10 write name of job |  | |  |  |  | | | |  | | \|__\|__\| | \|__\|__\|__\|__\| |
|  | | | |  |  |  | | | |  | | \|__\|__\| | \|__\|__\|__\|__\| |
|  |  |  |  |  |  |  | | | |  | | \|__\|__\| | \|__\|__\|__\|__\| |
| **Socioeconoimc status** | | | | | | | | | | | |  | |
| 17 | Household assets: (tick all that apply) | TV [ ] | | Radio [ ] | | | Car [ ] | | Pressure Cooker [ ] | | |  |  |
|  |  | Land [ ] | | House [ ] | | | Business [ ] | | Guest room [ ] | | |  |  |
| 18 | Amount of land owned: | \|__\|__\|jeribs | | 19. Number of people in household: | | | \|__\|__\| people | | | | |  |  |
| 20 | Number of rooms: | \|__\|__\| rooms | | 21. Is CHW the primary wage earner in their household? | | | Yes | | \|__\| | | |  |  |
|  |  |  |  |  |  |  | No | | \|__\| | | |  |  |

***Instructions for use****: The aim of this survey is to understand the kind of activities that a CHW carries out during a typical working week. The study registrar should explain the following to the CHW –*

- *This is not a test, we need to get an idea of what kind of things the CHWs do and how long they spend doing each activity.*
- *We are interested in what activities they can do during a typical week as well as what activities they are not able to do during a typical week, for instance if they do not do a particular activity, perhaps because they do not have enough time, this is useful information.*
- *The CHWs should be completely confident that this information is confidential and will not be shared with their employers.*

Top of Form

| **CHW details** | |
| --- | --- |
| 1. CHW ID number: CRT _ Clinic ID_ HP #_CHW # | CRT -\|__\|__\|__\| - \|__\|__\|-\|__\| |
| 1. Health-post MoPH number: | \|__\|__\|__\|__\|__\| |
| **CHW workload** | |
| 1. In a typical week, how many days of the week do you conduct CHW activities, for instance, every day or less than every day? (0-7 days) | \|__\|__\|days |
| 1. On a typical day when you work as a CHW, how many hours do you spend on CHW activities? | \|__\|__\| hrs \|__\|__\|mins |

| **A) Has the CHW ever conducted the following activity as part of their role?** | | **B) If yes, in the previous week, how many times did the CHW carry out this activity?** | **C) When CHW last carried out this activity / consultation – how many hours (or minutes) did the activity take?** | **D) When the CHW last carried out this activity - where did it take place?** | |
| --- | --- | --- | --- | --- | --- |
| 1. Consultation for pregnancy | Yes[figure not shown] No [figure not shown] | \|__\|__\| times | \|__\|__\| hrs \|__\|__\|mins | CHW’s home | [figure not shown] |
|  |  |  |  | Community centre | [figure not shown] |
|  |  |  |  | Nearest clinic | [figure not shown] |
|  |  |  |  | Patient’s home | [figure not shown] |
|  |  |  |  | Outside in open | [figure not shown] |
|  |  |  |  | Other | [figure not shown] |
| 1. Consultation for a sick adult (excluding pregnant mothers) | Yes[figure not shown] No [figure not shown] | \|__\|__\| times | \|__\|__\| hrs \|__\|__\|mins | CHW’s home | [figure not shown] |
|  |  |  |  | Community centre | [figure not shown] |
|  |  |  |  | Nearest clinic | [figure not shown] |
|  |  |  |  | Patient’s home | [figure not shown] |
|  |  |  |  | Outside in open | [figure not shown] |
|  |  |  |  | Other | [figure not shown] |
| 1. Consultation for a sick child (excluding pregnant mothers) | Yes[figure not shown] No [figure not shown] | \|__\|__\| times | \|__\|__\| hrs \|__\|__\|mins | CHW’s home | [figure not shown] |
|  |  |  |  | Community centre | [figure not shown] |
|  |  |  |  | Nearest clinic | [figure not shown] |
|  |  |  |  | Patient’s home | [figure not shown] |
|  |  |  |  | Outside in open | [figure not shown] |
|  |  |  |  | Other | [figure not shown] |
| 1. Treatment for accident / trauma / other injury | Yes[figure not shown] No [figure not shown] | \|__\|__\| times | \|__\|__\| hrs \|__\|__\|mins | CHW’s home | [figure not shown] |
|  |  |  |  | Community centre | [figure not shown] |
|  |  |  |  | Nearest clinic | [figure not shown] |
|  |  |  |  | Patient’s home | [figure not shown] |
|  |  |  |  | Outside in open | [figure not shown] |
|  |  |  |  | Other | [figure not shown] |
| 1. Vaccine program activity | Yes[figure not shown] No [figure not shown] | \|__\|__\| times | \|__\|__\| hrs \|__\|__\|mins | CHW’s home | [figure not shown] |
|  |  |  |  | Community centre | [figure not shown] |
|  |  |  |  | Nearest clinic | [figure not shown] |
|  |  |  |  | Patient’s home | [figure not shown] |
|  |  |  |  | Outside in open | [figure not shown] |
|  |  |  |  | Other | [figure not shown] |
| 1. Family planning | Yes[figure not shown] No [figure not shown] | \|__\|__\| times | \|__\|__\| hrs \|__\|__\|mins | CHW’s home | [figure not shown] |
|  |  |  |  | Community centre | [figure not shown] |
|  |  |  |  | Nearest clinic | [figure not shown] |
|  |  |  |  | Patient’s home | [figure not shown] |
|  |  |  |  | Outside in open | [figure not shown] |
|  |  |  |  | Other | [figure not shown] |
| 1. Delivering bed nets to houses | Yes[figure not shown] No [figure not shown] | \|__\|__\| times | \|__\|__\| hrs \|__\|__\|mins | CHW’s home | [figure not shown] |
|  |  |  |  | Community centre | [figure not shown] |
|  |  |  |  | Nearest clinic | [figure not shown] |
|  |  |  |  | Patient’s home | [figure not shown] |
|  |  |  |  | Outside in open | [figure not shown] |
|  |  |  |  | Other | [figure not shown] |
| 1. Taking part in health committee meetings | Yes[figure not shown] No [figure not shown] | \|__\|__\| times | \|__\|__\| hrs \|__\|__\|mins | CHW’s home | [figure not shown] |
|  |  |  |  | Community centre | [figure not shown] |
|  |  |  |  | Nearest clinic | [figure not shown] |
|  |  |  |  | Patient’s home | [figure not shown] |
|  |  |  |  | Outside in open | [figure not shown] |
|  |  |  |  | Other | [figure not shown] |
| 1. Filling in MAR reports | Yes[figure not shown] No [figure not shown] | \|__\|__\| times | \|__\|__\| hrs \|__\|__\|mins | CHW’s home | [figure not shown] |
|  |  |  |  | Community centre | [figure not shown] |
|  |  |  |  | Nearest clinic | [figure not shown] |
|  |  |  |  | Patient’s home | [figure not shown] |
|  |  |  |  | Outside in open | [figure not shown] |
|  |  |  |  | Other | [figure not shown] |
| 1. Health education and awareness | Yes[figure not shown] No [figure not shown] | \|__\|__\| times | \|__\|__\| hrs \|__\|__\|mins | CHW’s home | [figure not shown] |
|  |  |  |  | Community centre | [figure not shown] |
|  |  |  |  | Nearest clinic | [figure not shown] |
|  |  |  |  | Patient’s home | [figure not shown] |
|  |  |  |  | Outside in open | [figure not shown] |
|  |  |  |  | Other | [figure not shown] |
| 1. Attending training sessions | Yes[figure not shown] No [figure not shown] | \|__\|__\| times | \|__\|__\| hrs \|__\|__\|mins | CHW’s home | [figure not shown] |
|  |  |  |  | Community centre | [figure not shown] |
|  |  |  |  | Nearest clinic | [figure not shown] |
|  |  |  |  | Patient’s home | [figure not shown] |
|  |  |  |  | Outside in open | [figure not shown] |
|  |  |  |  | Other | [figure not shown] |

| **CHW travel to the health clinic** | |
| --- | --- |
| 1. How long does it take you to get to your clinic? | \|__\|__\| hrs \|__\|__\| mins |
| 1. What transport do you normally use to get to the clinic? | __________________________ |
| 1. Last week, how many times did you go to the clinic? | \|__\|__\| times |

Bottom of Form

Top of Form

Bottom of Form

## Annex 2: Revised IMCI algorithm for treatment of fever at community level:

Source: DRAFT Strategy for Community Based Management of Malaria, WHO/MoPH, 2011.

[figure not shown]

Algorithm for managing common childhood illness at community level as part of the Community IMCI strategy^[[4]](#footnote-4)^.

## Annex 3: Evaluation indicators for National CBMM strategy (benchmarks for Arm 2).

| # | **Indicator** | **Data Requirement** | **Notes (added by the Investigators)** |
| --- | --- | --- | --- |
| 1 | Number of RDT received in the country by implementing agencies | Number of RDTs received in the country per year by funding and implementing agencies | Not for use in the evaluation |
| 2 | Number of RDT delivered to BPHS implementers at provincial level | Number of RDTs delivered at provincial level  to BPHS implementers | Not for use in the evaluation |
| 3 | Proportion of targeted BHCs and HSCs reporting no RDT stockouts | **Numerator:** Number of targeted BHCs and HSCs reporting no RDT stockouts per month **Denominator:** Number of targeted BHCs and HSCs submitting monthly stock reports on RDT | Not for use in the evaluation – the trial will include the assumption that RDTs are available in the clinics in abundance and they will be provided with sufficient tests to reach the sample size requirements |
| 4 | Proportion of targeted HPs reporting no RDT stockouts | **Numerator:** Number of targeted HPs reporting no RDT stockouts on tally sheets  **Denominator:** Number of targeted HPs submitting tally sheets with RDT stocks | As above |
| 5 | Number of ACT received in the country by implementing agencies | Number of ACTs received in the country per year by funding and implementing agencies | Not used in the evaluation |
| 6 | Number of ACT delivered to BPHS implementers at provincial level | Number of ACTs delivered at provincial level  to BPHS implementers (every 6 months) | Not used in the evaluation |
| 7 | Proportion of targeted BHCs and HSCs reporting no ACT stockouts | **Numerator:** Number of targeted BHCs and HSCs reporting no ACT stockouts per month **Denominator:** Number of targeted BHCs and HSCs submitting monthly stock reports on ACT | Not used in the evaluation |
| 8 | Proportion of targeted HPs reporting no ACT stockouts | **Numerator:** Number of targeted HPs reporting no ACT stockouts on tally sheets  **Denominator:** Number of targeted HPs submitting tally sheets with ACT stocks | Not used in the evaluation |
| 9 | Proportion of malaria cases confirmed by RDT in targeted BHCs and HSCs | **Numerator:** Number of reported malaria cases confirmed by RDT in targeted BHCs and HSCs **Denominator:** All reported malaria cases from targeted BHCs and HSCs | Not used in the evaluation |
| 10 | Proportion of malaria cases confirmed by RDT in targeted Health Posts | **Numerator:** Number of reported malaria cases confirmed by RDT in targeted BHCs, HSCs and Health Posts  **Denominator:** All reported malaria cases from targeted BHCs, HSCs and Health Posts | Included in the evaluation.  The denominators will be (a) the number of suspected malaria cases (fever) and (b) the number of PCR confirmed malaria cases.  Draft Target: 85% |
| 11 | Proportion of reported falciparum cases confirmed by RDT treated with ACTs in targeted BHCs and HSCs | **Numerator:** Number of reported falciparum cases confirmed by RDT treated with ACTs in targeted BHCs and HSCs  **Denominator:** All reported falciparum cases confirmed by RDT from targeted BHCs and HSCs | Included in the evaluation.  The denominators will be (a) the number of suspected malaria cases (fever) and (b) the number of PCR confirmed malaria cases.  Draft Target (taken from national malaria strategic plan): 90% |
| 12 | Proportion of reported falciparum cases confirmed by RDT treated with ACTs in targeted Health Posts | **Numerator:** Number of reported falciparum cases confirmed by RDT treated with ACTs in targeted BHCs, HSCs and Health Posts  **Denominator:** All reported falciparum cases confirmed by RDT from targeted BHCs, HSCs and Health Posts | Included in the evaluation.  The denominators will be (a) the number of suspected malaria cases (fever) and (b) the number of PCR confirmed malaria cases.  Draft Target (taken from national malaria strategic plan): 90% |
| 13 | Proportion of reported non-falciparum cases confirmed by RDT treated with chloroquine + primaquine in targeted BHCs and HSCs | **Numerator:** Number of reportd non-falciparum cases confirmed by RDT treated with chloroquine + primaquine in targeted BHCs and HSCs  **Denominator:** All reported non-falciparum cases confirmed by RDT from targeted BHCs and HSCs | Included in the evaluation.  The denominators will be (a) the number of suspected malaria cases (fever) and (b) the number of PCR confirmed malaria cases.  Draft Target (taken from national malaria strategic plan): 90% |
| 14 | Proportion of reported non-falciparum cases confirmed by RDT treated with chloroquine in targeted Health Posts | **Numerator:** Number of reportd non-falciparum cases confirmed by RDT treated with chloroquine in targeted Health Posts  **Denominator:** All reported non-falciparum cases confirmed by RDT from targeted HPs | Included in the evaluation.  The denominators will be (a) the number of suspected malaria cases (fever) and (b) the number of PCR confirmed malaria cases.  Draft Target (taken from national malaria strategic plan): 90% |

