## Laboratory Methods:

### RDT Selection:

In-line with national policy the study will use: CareStart™ 3-line Pf (HRP2) + Pan (pLDH) malaria rapid diagnostic test (AccessBio, New Jersey, USA). Recently, this test was evaluated in Afghanistan and found to have accuracy >95% and to match the WHO criteria for accuracy.

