### PCR Evaluation:

Filter paper blood spots will be collected in triplicate for all patients enrolled in the study and processed in Kabul. As described previously, DNA will be extracted with the crude TE buffer method[1], while the Mangold melt-curve real-time PCR[2] will be run to detect *Plasmodium* sp. DNA and discriminate between species. The assay will not be performed quantitatively. A random selection of 10% of all filter paper blood spots will be sent to the LSHTM malaria reference centre for re-evaluation by alternative PCR methods and quality control.

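### Annex 3, indicator 10: under the PCR-confirmed denominator the RDT numerator is not limited to PCR-positive patients, so false-positive tests raise the score and it can exceed 100%

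*Protocol*

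**What the plan says.** Annex 3 takes over the national community-management indicators as benchmarks for Arm 2. Indicator 10 is titled "Proportion of malaria cases confirmed by RDT in targeted Health Posts". Its national numerator is "Number of reported malaria cases confirmed by RDT in targeted BHCs, HSCs and Health Posts" and its national denominator is "All reported malaria cases from targeted BHCs, HSCs and Health Posts".

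In the column of notes that the investigators added, the indicator is taken into the evaluation with new denominators: "The denominators will be (a) the number of suspected malaria cases (fever) and (b) the number of PCR confirmed malaria cases". The same note gives "Draft Target: 85" per cent. It does not alter the numerator, and it does not say whether the target belongs to (a) or to (b). The same denominator sentence stands at indicators 11 to 14, each with a draft target of 90%.

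Other parts of the protocol that bear on this:

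- Section 2.9.4: "Filter paper blood spots will be collected in triplicate for all patients enrolled in the study". PCR status is therefore planned for enrolled patients, while the numerator speaks of reported cases.
- Section 2.9.1: "this test was evaluated in Afghanistan and found to have accuracy >95" per cent. The figure is not split into sensitivity and specificity and is not given for CHW use.
- Sections 2.6.1 and 2.6.2: the primary outcome is defined against PCR, and RDT sensitivity and specificity against PCR are a secondary outcome.
- Section 2.6.3: the indicators are still in draft and may change.

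**The concern.** In the national form, every RDT-confirmed case is also a reported case, so the numerator sits inside the denominator and the result is a true proportion. The investigators' note breaks this for (b) by exchanging the denominator alone. A patient who is RDT-positive and PCR-negative now enters the numerator and can never enter the denominator. A false-positive test is scored as a success.

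What is at stake is how Arm 2 is described against its own benchmark. Set beside 85%, a figure labelled as the proportion of malaria confirmed by RDT would be read as detection of true cases. Under (b) it mixes detection with false positives, and the mix depends on how common malaria is among the patients tested. The same report would also carry RDT sensitivity against PCR, which could contradict it.

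**Working it through.** The 85% is a set target, not a calculated figure, so there is nothing to reproduce. The check is what the written ratio equals.

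**Inputs.** Let s be RDT sensitivity, c specificity and p the PCR positivity among tested patients. The protocol states none of the three for CHW use. Assumed: c = 95% (a reading of the overall accuracy figure in Section 2.9.1) and c = 98% for comparison; p from 5% to 30%. The 16% point equals 2518/15719 in the Section 2.8.2 table. That is a share of treatments given, not PCR positivity, and is used only as an illustration.

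**Formulas for indicator 10.**

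- (b) as written: RDT-positive / PCR-positive = s + (1 − c)(1 − p)/p
- (b) with the numerator limited to PCR-positive patients: s
- (a): RDT-positive / suspected = s·p + (1 − c)(1 − p)

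The second term of the first line is the number of false positives per true case. Setting that line to 0.85 gives the sensitivity at which the target is met.

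| p | False positives per true case, c = 95% | s that suffices, c = 95% | s that suffices, c = 98% | Score (b) if s = c = 95% |
| --- | --- | --- | --- | --- |
| 5% | 0.05 × 0.95/0.05 = 0.95 | 0% | 47% | 190% |
| 10% | 0.05 × 0.90/0.10 = 0.45 | 40% | 67% | 140% |
| 16% | 0.05 × 0.84/0.16 = 0.26 | 59% | 74.5% | 121% |
| 30% | 0.05 × 0.70/0.30 = 0.12 | 73% | 80% | 107% |

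The last column shows that the ratio is not a proportion even when the test performs well.

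**In counts.** Assume 1000 tested, p = 10%, s = 40%, c = 95%. There are 100 PCR-positive patients, 0.40 × 100 = 40 true positives and 0.05 × 900 = 45 false positives, so 85 are RDT-positive.

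- (b) as written: 85/100 = 85%
- (b) limited to PCR-positive patients: 40/100 = 40%
- (a): 85/1000 = 8.5%

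**Denominator (a).** This one contains its numerator. With s = c = 100% it equals p, so a perfect test reaches 85% only if at least 85% of suspected cases are PCR-positive.

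**Indicators 11 to 14 under (b).** Their numerators also lack a PCR condition, but they require the stated treatment as well, and (b) counts PCR-confirmed malaria of every species. Section 1.2 puts falciparum at about 5–10% of malaria cases. A perfect test with every falciparum case treated as indicators 11 and 12 require therefore scores 5–10% against 90%. Adding an assumed 1% false falciparum result, with all such patients treated, contributes 0.01 × 0.95/0.05 = 19 points at p = 5%, giving 24–29%. At p = 16% it contributes about 5 points, giving 10–15%. For 13 and 14 the same denominator caps a perfect programme at 90–95%.

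**The case against.** The strongest reply is that the word proportion in the title implies a subset, so that with PCR-confirmed cases as denominator the natural meaning is the share of those cases that were RDT-confirmed. That may well be the intention. But the numerator is spelled out, it says something else, and no text limits it. An analyst who follows the annex would compute the unrestricted ratio.

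The second reply is that little depends on it. This stands in part. The indicators are a draft benchmark for Arm 2. Section 2.5.6 mentions criteria for running Phase 2 but does not name indicator 10 among them. Poor detection would still show in the PCR-based outcomes of Sections 2.6.1 and 2.6.2. These points limit the reach of the error; they do not make the ratio correct.

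A reader might go further and infer that Arm 2 can pass its 85% target while missing most malaria. The documents do not support that as a general statement:

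- The target is not tied to (b), and in the worked case (a) reads 8.5%.
- Of the eight combinations of positivity and specificity in the table, the sensitivity that suffices is below 50% in only three (0%, 40% and 47%). In the other five it is 59% to 80%.
- Missed positives and invalid tests lower the ratio; only false positives raise it. Section 1.2 reports invalid tests and few cases adequately detected in earlier CHW programmes, and says nothing of false positives.

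Nor does false success carry over readily to indicators 11 and 12. Under (b) as written, the all-species denominator pulls their scores far below target.

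**Conclusion.** The point holds for indicator 10 under denominator (b). As written, the score is sensitivity plus false positives per true case. It is not the share of true malaria confirmed by RDT, and it can exceed 100%. That conclusion is algebra and needs no assumption beyond some tests being false positive.

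The size does rest on assumptions, because PCR positivity and CHW-level accuracy are not given. At 95% specificity, 85% is reached with sensitivity of 40% at 10% positivity and 73% at 30%; at 98% specificity the corresponding figures are 67% and 80%. The unassigned target is a related gap: the same programme can meet 85% under (b) and fall far short under (a).

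Indicators 11 to 14 share the unrestricted numerator. In 11 and 12 the all-species denominator is clearly the larger fault. In 13 and 14 it leaves a perfect programme little or no room above the 90% target. The error should be corrected before the Arm 2 evaluation is reported, but it does not touch the trial's primary comparison.

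**What to change.** In the notes to indicators 10 to 14:

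- State that under (b) the numerator counts only enrolled patients who are PCR-positive and also RDT-confirmed and, in 11 to 14, treated as the indicator states.
- In 11 to 14, restrict both numerator and denominator under (b) to the matching PCR species.
- State which denominator, (a) or (b), each draft target applies to.
- Report RDT-positive, PCR-negative patients separately as a count.

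The cost is a few sentences in Annex 3. RDT result and treatment are already recorded per patient (Section 2.7.2 and Annexes 4 and 5), and blood spots for PCR are planned for all enrolled patients, so no new data are needed. There are two drawbacks. The reported 10(b) figure will be less favourable, and it will overlap with the RDT sensitivity outcome in Section 2.6.2, so the report should say how the two relate.

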## Scientific Rationale:

Targeting of antimalarial drugs is an important priority for delivery of effective treatments and requires parasitological diagnosis of malaria parasites and prescription of appropriate treatment. In areas where cases result from two or more species (typically *Plasmodium falciparum* and *P. vivax*) treatments for the two species differ. Because falciparum malaria has developed resistance to chloroquine, which remains effective against vivax malaria, identification of the species of malaria is vital for targeting ACTs.

Most malaria in Afghanistan is caused by vivax, which is a minority (although significant) cause of febrile illness. A few (around 5-10%) of cases are caused by falciparum malaria, which is treated with more expensive artemisinin combination therapy drugs (ACT). Identifying these few cases of falciparum and targeting the more expensive drugs at the few cases that occur is the major challenge. Mistreatment of falciparum as vivax (i.e. with chloroquine) could lead to poor treatment outcomes, where vivax treated as falciparum (i.e. with the more expensive ACT drugs) wastes expensive drugs. This places great importance on access to accurate diagnosis that can distinguish between the species.

Current research conducted at clinic basic health centre level shows that when parasitological diagnosis (using either RDTs or microscopy) is implemented at the clinic level, there is an improvement in treatment accuracy (i.e. the proportion of patients who are correctly treated) when compared to clinical diagnosis only (i.e. where there is no identification of parasites). However, despite this improvement around 50% of patients who are negative for malaria parasites are still treated with antimalarial drugs. The research conclusions show that improving the targeting of drugs requires not only the implementation of parasitological diagnosis, but also a change in prescriber behaviour. The over treatment for malaria, despite negative laboratory results, wastes drugs, reduces the cost-effectiveness of the diagnostic method, and (most importantly) leads to mistreatment of other causes of fever.

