## Outcomes:

The trial outcomes are presented below. In addition, the RDT arm (arm 2) will be subjected to an interim evaluation for which outcomes are also presented.

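### Annex 3 keeps the national 85% and 90% targets for indicators 10–14 but substitutes denominators under which most of them cannot be met

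*Protocol*

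**What the plan says.** Annex 3 of the protocol, presented as the benchmarks for Arm 2, lists national programme indicators and marks 10–14 for use in the evaluation. In the national definitions numerator and denominator belong together:

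- Indicator 10 divides RDT-confirmed malaria by all reported malaria.
- Indicators 11 and 12 divide RDT-confirmed falciparum cases given ACT by RDT-confirmed falciparum cases. For 11 the denominator is "All reported falciparum cases confirmed by RDT from targeted BHCs and HSCs".
- Indicators 13 and 14 do the same for non-falciparum cases. For 14 the denominator is "All reported non-falciparum cases confirmed by RDT from targeted HPs".

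The notes column, added by the investigators, repeats one sentence for all five: "The denominators will be (a) the number of suspected malaria cases (fever) and (b) the number of PCR confirmed malaria cases". The targets follow directly: "Draft Target: 85" per cent for indicator 10 and "Draft Target (taken from national malaria strategic plan): 90" per cent for 11–14.

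Section 2.6 states that "the RDT arm (arm 2) will be subjected to an interim evaluation for which outcomes are also presented", and section 2.6.3 refers to Annex 3 for the indicators and targets. On case mix, section 1.2 says "Most malaria in Afghanistan is caused by vivax, which is a minority (although significant) cause of febrile illness" and "A few (around 5-10%) of cases are caused by falciparum malaria".

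**The concern.** A target has meaning only for the ratio it was set for. The note changes the ratio and leaves the target. For indicators 11–14 the numerator covers one species group, while denominator (b), as written, covers every species. Denominator (a) adds all the fevers that are not malaria, so indicator 10 over (a) is simply RDT positivity.

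The values reported for Arm 2 would then be governed largely by how common falciparum is among malaria cases and how common malaria is among fevers. A figure of about 5% beside a 90% target would read as poor care when it describes the case mix. Recommendations for community programmes are a stated objective (section 2.1), so a comparison of this kind should not reach readers in that form.

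**Working it through.** **Inputs**

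- f, the falciparum share of malaria: 5–10% (section 1.2).
- Vivax as a share of fevers: a minority (section 1.2), taken as under 50%. All non-falciparum malaria is treated as vivax.
- m, the malaria share of suspected cases: not given. From the two inputs above, m < 0.50/(1 − f), that is 0.50/0.95 = 52.6% at f = 5% and 0.50/0.90 = 55.6% at f = 10%. This assumes that suspected malaria has the case mix of fever; the note itself equates the two.
- Targets: 85% and 90% (Annex 3). They are external benchmarks, so the protocol contains no derivation to reproduce.

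**Reference case.** With the national denominators, perfect testing and treatment give 100% for all five indicators, so the targets are attainable there.

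**Ceilings with the substituted denominators** (perfect test, perfect treatment, no RDT false positives)

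| Indicator | Target | (a) suspected malaria (fever) | (b) PCR-confirmed, all species |
| --- | --- | --- | --- |
| 10 | 85% | m: below 52.6–55.6% | 100% |
| 11, 12 | 90% | m × f: below 2.6–5.6% | f: 5–10% |
| 13, 14 | 90% | m × (1 − f): below 50% | 1 − f: 90–95% |

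For 11–12 under (a): 0.526 × 0.05 = 0.026 and 0.556 × 0.10 = 0.056. Of the ten indicator–denominator pairs, seven cannot meet the target (five under (a), two under (b)), two are borderline (13 and 14 under (b)) and one is reachable (10 under (b)).

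**How much depends on m.** Under (a), indicators 11–12 cannot exceed f at any m, so they miss 90% regardless. Indicator 10 would need m of at least 85%. Indicators 13–14 would need m of at least 0.90/0.95 = 94.7% at f = 5%, and 100% at f = 10%. As a rough pointer only, the table in section 2.8.2 shows 2518 of 15719 listed treatments (16.0%) given for malaria: 47 of 5901 (0.8%) in Kunduz and 2471 of 9818 (25.2%) in Nangarhar. These are treatments, not PCR results. At m = 16% the ceilings under (a) would be 16%, 0.8–1.6% and 14.4–15.2%.

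**Imperfect sensitivity.** Section 2.9.1 gives only an accuracy above 95%. With sensitivity assumed to be 95%, indicators 13–14 under (b) reach 0.95 × 0.90 = 85.5% to 0.95 × 0.95 = 90.25%. They meet 90% only if f ≤ 1 − 0.90/0.95 = 5.3%.

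**False positives.** RDT-positive, PCR-negative patients enter the numerator but not denominator (b). With m = 10% and sensitivity and specificity both assumed to be 95%, indicator 10 under (b) is (0.10 × 0.95 + 0.90 × 0.05)/0.10 = 140%. Under (a) the same error changes little: at m = 55.6% with every true case detected, indicator 10 becomes 0.556 + 0.444 × 0.05 = 57.8%, still short of 85%.

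**The case against.** Five points can be made for the plan.

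1. **Denominator (b) may be meant per species.** Each row already names its species, so the note could mean PCR-confirmed cases of that species. Every target under (b) would then be attainable. The text does not settle this. The identical sentence serves indicator 10, where it must mean all species, and on either reading the targets under (a) stay out of reach.

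2. **The caps under (b) need an error-free test.** This stands. Take 1000 fevers with 10% malaria, 10% of that falciparum, and 5% of the 900 negatives read falsely as falciparum (all assumed). If all are given ACT, indicators 11–12 under (b) come to (10 + 45)/100 = 55%. The 5–10% cap is therefore conditional. However, a ratio that rises through misdiagnosis is a further reason not to set a target against it.

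3. **The material is openly draft.** Section 2.6.3 says the indicators may change. That caveat concerns the national strategy, whose denominators are sound. The mismatch is in the investigators' own column, and finalising the strategy would not remove it.

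4. **The trial has its own outcomes.** This stands. The primary outcome (section 2.6.1) and the falciparum–ACT secondary outcome (section 2.6.2) do not use Annex 3.

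5. **A reader might infer more than the document supports**: that all of indicators 10–14 are unreachable under either denominator, and that the Arm 2 interim evaluation would therefore fail or block Phase II. The first inference is contradicted by indicator 10 under (b) and by the 90–95% ceilings for 13–14. The second has no textual basis. No rule says that a missed target is a failure, and the Phase II criteria mentioned in section 2.5.6 are not linked to Annex 3.

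**Conclusion.** The notes column is wrong as written. Under (a) the targets for all five indicators, and under (b) as worded those for 11 and 12, cannot be met even with perfect testing and treatment. For 11–12 the gap is at least 80 percentage points (90% against at most 10%). Indicators 13–14 under (b) can only just be met, and indicator 10 under (b) can be met. Separately, every ratio under (b) has a numerator that is not a subset of its denominator and so is not a true proportion.

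The figures rest on falciparum at 5–10% of malaria, vivax below half of suspected cases, and no RDT false positives. The result under (a) is not sensitive to the last of these; the cap for 11–12 under (b) is. The consequence is limited to the Arm 2 benchmark comparison, which would report shortfalls unrelated to performance. The primary outcome is untouched.

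**What to change.** Edit the notes column of Annex 3 for indicators 10–14:

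- Apply the 85% and 90% targets only to the national denominators: reported malaria for 10, RDT-confirmed falciparum for 11–12, RDT-confirmed non-falciparum for 13–14.
- Redefine (b) as PCR-confirmed cases of the species in the numerator (all species for 10), and count in the numerator only patients who are also in that denominator. The ratio is then a true proportion with a ceiling of 100%, or 95% if RDT sensitivity is 95%. It combines test sensitivity with treatment and should be labelled so.
- Drop (a), or report it descriptively with no target.

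The cost is a text edit and a small change to the tabulation. RDT results, treatment given and PCR results are already collected, so no new data are needed. What is lost is the direct comparison of the PCR-based ratios with the national targets, which was not valid in any case.
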